### Data collection

All participants enrolled in the trial are asked to complete a paper questionnaire at the baseline clinic appointment and a posted questionnaire after 2 weeks, 2 months, 4 months and 6 months. Questionnaires will capture data on all outcome measures (Table 2).

Baseline data collection includes: demographics (date of birth, gender, marital status); hip pain questions: uni/bilateral, duration; previous hip injection; participant treatment preference and expectations; comorbidity; self-reported height and weight (Body Mass Index - BMI), other musculoskeletal pain (Body manikin) [22] and anxiety and depression – Generalised Anxiety Disorder (GAD) and Patient Health Questionnaire 8 [23, 24].

For participants receiving I2 and I3, bilateral ultrasound images are stored, and scored on the presence or absence of synovitis and effusion. Participants are also asked which injection they think they received.

Non-responders to the 2-week follow-up postal questionnaire are sent a repeat questionnaire and PIL after 10 calendar days. Those who do not respond to the repeat questionnaire within 10 days are telephoned by the Research Nurse (who will remain blind to group allocation), in order to try to capture key primary outcome data and to minimise missing data. A postal MDC form is mailed to the participant if the participant has not been contacted after 5 phone-call attempts.

At other follow-up time-points, non-responders are sent a reminder postcard after 10 days. Those who do not respond to the reminder postcard are sent a repeat questionnaire and Participant Information Sheet with a further covering letter after a further 10 days. Non-responders to the repeat questionnaire are telephoned by the Research Nurse (blind to treatment allocation) 10 days later. A postal MDC form are mailed to the participant if the participant has not been contacted after 5 phone-call attempts.

The flow of events as participants proceed through the trial is outlined in (Fig. 1) and the timing of key events outlined in Table 3.

**Fig. 1 Fig1:**
[figure not shown]
Flow of participants through trial

**Table 3 Tab3:** Participant Timeline

Visits	Pre-Baseline	Baseline Day 0	Randomisation Day 0	Intervention Day 0	2-week follow-up	2-month follow-up	4 month follow-up	6-month follow-up
				Duration of Intervention				
Events								
Brief telephone screening (identified via route 3)	✓							
Consent to eligibility screening assessment (route 3)		✓						
Eligibility Screening		✓						
Full informed consent by researcher/ research assistant		✓						
Randomisation			✓					
Participant Questionnaire (see Table 1)		✓			✓	✓	✓	✓
Web-based randomisation			✓					
Administration of study intervention				✓				
SAE reporting				✓	✓	✓	✓	✓
Expedited reporting (< 24 h) of Suspected Unexpected Serious Adverse Reactions (SUSARs)				On going				

### Sample size

To address the objectives of the trial, 204 participants (68 in each arm) need to be recruited over a 29-month period [amended since trial registration, see Table 1 and ‘Progress of trial’]. To address the primary objective, the analysis will be based on comparisons of participants’ ‘average’ follow-up pain NRS scores, based on a random effects linear repeated-measures model, with four follow-ups and postulated correlations of 0.5 for repeat-measures and 0.2 for baseline-outcome. A sample size of 136 (68 per arm) provides 80% power (5% two-tailed significance) to detect a minimum difference of 1 point in mean pain NRS score (anticipated SD of about 2.5; effect size of 0.4) between I1 and I2 across the 6-month follow-up period, allowing for 15% loss to follow-up. As the trial also evaluates I3 (against I1), there are three groups of interest and hence 204 participants are needed.

### Statistical methods

The analysis will be undertaken according to an analysis plan agreed with the TSC and DMC, incorporating statistical analysis, health economics and qualitative analysis.

The main statistical analysis is based on reporting guidelines for the design and conduct of parallel-arm trials [25]. The main treatment analysis will be conducted blinded to treatment allocation and will be analysed on an intention to treat (ITT) approach with all randomised participants retaining their original randomised group. Estimation through linear mixed modelling takes account of missing data (under the missing at random (MAR) missingness assumption). Analysis will be adjusted for baseline covariates (pain, age and gender). Additional sensitivity analysis will address the robustness of the findings to deviation from the MAR assumption – specifically through considering plausible ‘missing not at random’ (MNAR) scenarios.

Key baseline characteristics of participants in the three treatment groups will be presented to illustrate comparability. The linear mixed model will be used to derive estimates of ‘average’ pain across the four time points (thus reflecting summary pain assessment across the full follow-up period) as well as estimates of pain at each time point (by modelling the interaction of group by time). In each evaluation, a random-slope model will be preferred (to a random-intercept model) if the goodness-of-fit of the model is significantly improved through time-projected random-slope specification. Statistical significance is at the 5% probability level (two-tailed). The collection of data and statistical analysis will be performed blinded to treatment allocation. The primary clinical evaluation will be a comparison of pain NRS scores over the 6-month follow-up period (with repeated measures at 2 weeks and 2, 4 and 6 months) between those treated with best current treatment plus corticosteroid and lidocaine injection, and those treated with best current treatment alone.

The secondary clinical evaluations will include: evaluation of pain NRS score differences between groups at each of the individual time points (2 weeks, 2 months, 4 months and 6 months) as well as between-group comparison of secondary outcome measures over the 6-month follow-up period. Mixed models for repeated measures (MMRM) will be through linear-regression in respect of numerical outcomes, and logistic-regression in relation to categorical outcome measures. A number of follow-up data are anticipated to be retrieved through minimum data collection, and therefore we will use multiple imputation (MI) using chain equations [26] to impute missing secondary outcome data – the prediction models will include baseline variables and the (primary) pain outcome measure as predictors. MI, similar to mixed modelling, estimates effect on the basis of an MAR missingness mechanism. Estimation of the primary outcome measure based on MI evaluation will be carried out as a sensitivity analysis of the main MMRM analysis. In addition, an MI analysis incorporating plausible deviations from ignorable missingness will be considered in respect of sensitivity analysis of the primary outcome to MNAR missing data.

The primary analyses will be adjusted for the following baseline covariates: pain score, age and gender (and EQ5D for health economic evaluation). Estimates of clinical effect will be shown as mean (SDs) differences (for numerical outcomes) and odds ratios (for dichotomous outcomes), with 95% confidence intervals (CI). As previously stated, regression analysis will be based on a linear model for numerical outcomes and binary logistic model for dichotomous outcomes with a random-effects component being added to the model for repeated measures data, to take into account the intra-cluster correlation. To help in interpreting the size of the estimated clinical effect for the between-group difference in pain (overall and at individual time points) we will calculate the standardised mean difference (‘effect size’) which is the ratio of the estimated mean difference to the standard deviation of pain scores in the total randomised population. For all evaluations of the primary outcome, we will present mean and 95% confidence interval estimates. The number needed to treat (NNT) with 95% CI will be calculated in respect of the comparison between best current treatment plus corticosteroid and 1% lidocaine hydrochloride injection and best current treatment alone [27].

Exploratory subgroup analysis will include evaluation of variables such asParticipants’ expectations regarding treatment responseParticipants’ treatment preferenceIllness perceptionsAdherence to best current treatmentPresence of synovitis or effusion on ultrasoundBMIDuration of symptomsSeverity of symptoms

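### The predictors named for imputing secondary outcomes leave out randomised arm; applied as written, the list biases the between-arm differences, usually toward zero

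*Protocol article*

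**What the plan says.** Under Statistical methods, the protocol article gives the reason for imputing: "A number of follow-up data are anticipated to be retrieved through minimum data collection". It follows with the method and target, "we will use multiple imputation (MI) using chain equations [26] to impute missing secondary outcome data", and then the predictors: "the prediction models will include baseline variables and the (primary) pain outcome measure as predictors". It adds that "MI, similar to mixed modelling, estimates effect on the basis of an MAR missingness mechanism".

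The estimates that use these data are arm contrasts, described as "between-group comparison of secondary outcome measures over the 6-month follow-up period". The Secondary objectives ask for them for corticosteroid injection against best current treatment alone and against lidocaine injection.

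Under Data collection, non-responders who have had the repeat questionnaire are telephoned "in order to try to capture key primary outcome data and to minimise missing data". Records with pain observed and secondary outcomes missing are therefore an expected pattern.

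Two further statements bear on the point. The article says that "The collection of data and statistical analysis will be performed blinded to treatment allocation", and that "The analysis will be undertaken according to an analysis plan agreed with the TSC and DMC". That analysis plan is not shown.

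**The concern.** An imputation model should contain every term whose effect the analysis model then estimates. Here the analysis estimates the effect of arm, and the predictors named do not include arm. A model without arm draws missing values on the assumption that, given baseline and pain, the arms do not differ. Observed pain carries part of the arm effect into the imputed values, but only the part that runs through pain.

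Missing at random does not protect against this. It describes how data go missing and does not repair an imputation model that lacks a term. The outcomes at stake are the secondary ones, such as function, stiffness, sleep, self-efficacy and general health. The effect is largest for those only loosely related to pain.

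**Working it through.** **The plan's own figures.** The article gives no figure for imputation bias, so there is none to reproduce. Three inputs are borrowed from its Sample size section, which does reproduce. The variance factor is (1 + 3 × 0.5)/4 − 0.2² = 0.585. Then 2 × 0.585 × (1.960 + 0.842)²/0.4² = 57.4 per arm, and 57.4/0.85 = 67.5, rounded up to 68. Nothing below changes that sample size.

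**Inputs.**
- From the article: effect size 0.4 (stated for pain), baseline-outcome correlation 0.2 (stated for pain), 15% loss to follow-up.
- Assumed: secondary effect dY = 0.4 SD; pain effect dP = 0, 0.4 or 0.8 SD; within-arm correlation rho between pain and the secondary outcome; share imputed m; the 0.2 baseline correlation also holds for the secondary outcome; data missing completely at random; pain observed in every imputed record; one time point; two equal arms.

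**Formula.** With within-arm SDs of 1, the slope of the outcome on pain given baseline, with arm left out, is

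b = (rho − 0.04 + dY·dP/4) / (1 − 0.04 + dP²/4),

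where 0.04 = 0.2² and 1/4 is the variance of a balanced arm indicator. Imputed records then differ between arms by b·dP. The estimate is (1 − m)·dY + m·b·dP, and the relative bias is m·(b·dP/dY − 1).

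**Equal effects (dP = dY = 0.4).** Here dY·dP/4 = dP²/4 = 0.04, so b = rho and the relative bias is −m(1 − rho).

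**Pain unaffected (dP = 0).** Then b·dP = 0, and the bias equals the whole share imputed, −m.

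**Pain effect twice the secondary effect (dP = 0.8).**
- At rho = 0.5, b = 0.54/1.12 = 0.482 and b·dP = 0.386, close to the true 0.4.
- At rho = 0.8, b = 0.84/1.12 = 0.75 and b·dP = 0.60, above 0.4.

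| dP | rho | m | Formula, arm omitted | Simulation, arm omitted |
|---|---|---|---|---|
| 0.4 | 0.5 | 15% | 0.370 (−7.5%) | 0.370 (−8%) |
| 0.4 | 0.5 | 25% | 0.350 (−12.5%) | 0.347 (−13%) |
| 0.4 | 0.5 | 40% | 0.320 (−20%) | 0.324 (−19%) |
| 0.4 | 0.6 | 25% | 0.360 (−10%) | about 0.36 (−9%)* |
| 0.4 | 0.3 | 25% | 0.330 (−17.5%) | about 0.33 (−18%)* |
| 0 | 0.5 | 25% | 0.300 (−25%) | 0.302 (−25%) |
| 0.8 | 0.5 | 25% | 0.396 (−1%) | 0.397 (−1%) |
| 0.8 | 0.8 | 25% | 0.450 (+12.5%) | 0.453 (+13%) |

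The simulations used 400,000 records. Those marked * imputed from pain without a baseline variable; the others included one.

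**Arm included.** The imputation model then reproduces dY in the imputed records, so the bias is zero. In simulation the estimate was 0.39 to 0.41 in every scenario.

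**The case against.** The strongest reply is that the defect is read from silence. The article says what the prediction models will include; it does not say that the list is complete or that arm is excluded. It is a condensed report, and the full imputation specification normally sits in an analysis plan, which exists or is planned here. This stands in part: a reader might infer that the trial has decided to leave arm out, and the text does not support that. But the article does not leave the model open either. It names the method, the target and the predictors, and someone following that sentence would impute without arm.

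Other objections also stand:
- A reader might infer that the bias always runs toward zero. The last two rows of the table show it vanishing and reversing.
- A reader might infer that the outcome's own baseline value and its other follow-ups are missing too. Secondary outcomes such as WOMAC, SF-12, sleep and self-efficacy are measured at baseline, so baseline variables cover those values. Chained equations ordinarily use the other incomplete variables as predictors.
- The article does not say how many records will have pain without secondary outcomes. The absolute shift can be small: 0.03 SD at 15% imputed and correlation 0.5. Assuming about 58 evaluable per arm, the standard error of a single-time difference is √(2/58) = 0.19 SD.
- The calculation uses one pain score at one time. Extra follow-up scores that carry the arm effect would usually lessen the attenuation.

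None of this makes it sound to omit arm. A systematic bias that a named predictor removes should not be left to chance.

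**Conclusion.** The point holds in conditional form. The predictors named do not include randomised arm; if the list is applied as written, between-arm differences in secondary outcomes are biased, usually toward zero. Under equal effects of 0.4 SD on pain and the secondary outcome, the attenuation is about 8% with 15% imputed at correlation 0.5, and about 9% to 18% with 25% imputed at correlations of 0.6 down to 0.3. It reaches the full share imputed if pain shows no arm effect, and it vanishes or reverses if pain shifts much more than the secondary outcome. These sizes rest on the assumptions listed; the article itself supplies only the 0.4 effect for pain, the 0.2 baseline correlation and the 15% loss.

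A reader might carry the concern over to the primary result. The documents do not support that: the primary analysis is a linear mixed model of pain that does not use this imputation. Multiple imputation of pain is a sensitivity analysis only, and the predictor sentence is written for the secondary outcomes.

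**What to change.** Amend the sentence under Statistical methods, and its counterpart in the analysis plan, to say: *The imputation models will include coded randomised arm as a predictor, or imputation will be carried out separately within each coded arm, together with the baseline variables and the primary pain scores. The same rule applies to the multiple-imputation sensitivity analysis of the primary outcome.*

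Coded labels keep the analysis blinded, and the blinded mixed model already needs a group label to fit its group-by-time terms. The change is wording only and needs no new data. If arm is already intended, the sentence simply confirms it.

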### Economic evaluation

The health economic analysis will determine the cost-effectiveness of intra-articular corticosteroid injection for hip OA and best current treatment compared with best current treatment alone. A cost-consequence analysis will initially be reported, describing all important results relating to costs and outcomes. An incremental cost-utility analysis will be undertaken using participant responses to the EuroQoL EQ-5D-5 L questionnaire at baseline and each follow-up time-point, to calculate the cost per additional Quality-Adjusted Life Year (QALY) gained. The base-case analysis will adopt an NHS perspective and will include costs of the intervention and best current treatment, and other hip OA-specific health care utilisation. These may include primary care consultations, prescriptions, secondary care contacts and over-the-counter purchases by participants. Information on health care resource use and work absenteeism will be collected from participant questionnaires at six months. The robustness of the results will be explored using sensitivity analysis. Uncertainty in the confidence to be placed on the results of the economic analysis will be explored conducting a probabilistic sensitivity analysis to estimate cost effectiveness acceptability curves. Results from a broader societal perspective will also be presented, and will include participant-incurred and productivity costs in addition to heath care costs.

#### Qualitative study

A sample of responders to the 2-month follow up questionnaire are invited for interview to ask them about their experiences of participating in the trial and of living with hip osteoarthritis. Participants are sampled on a range of characteristics including age, gender, pain score and satisfaction with treatment. Participants are asked to complete and return a reply slip should they be interested in taking part in the interview. Interested participants are contacted by telephone to arrange a convenient time for the interview. Informed consent is taken prior to interview. Interviews are conducted either over the telephone or face-to-face depending on the participant’s preference. Recruitment is ongoing throughout the trial in phased batches.

#### Qualitative analysis

Data will be stored, and analysis managed, using NVivo software. All interviews are audio-recorded and fully transcribed verbatim and anonymised. An inductive approach will be taken to the analysis. Analysis is on-going from the first data collection time-point; the data is analysed thematically and a coding framework developed incorporating emergent themes. The data will undergo repeated comparisons through coding, recoding and memo writing in order to generate themes and concepts [28, 29], drawing on recognised techniques including the scrutiny of deviant cases, and checking for confirmatory or challenging evidence within the dataset [30]. Initial qualitative data analysis will be undertaken blind to the clinical trial results to facilitate an interpretive and inductive approach [31].

#### Patient and public involvement and engagement (PPIE)

This study was discussed with our large and active PPIE group prior to the funding submission. The group identified the importance of developing the research base for treatments that may provide an alternative to oral analgesia and that are less invasive than surgery. The group informed the design of the best current treatment intervention, as an active treatment arm involving advice on exercise and weight loss. The group have also piloted the time taken to complete baseline data collection and advised on content of the PIL and best current treatment information leaflets. The PPIE group will continue to work with the research team throughout the trial (for example in advising the dissemination plan).

#### Trial organisation and monitoring

The Trial Steering Committee met prior to ethics application in order to agree the final protocol, and at agreed time intervals over the course of the pilot trial. An independent Data Monitoring Committee (DMC) approved the protocol and reviews the safety of the trial. Detailed reports focusing on interim safety, recruitment and retention are prepared by Keele CTU at approximately 6 monthly intervals. All data collection, database design, data input and cleaning, as well as trial oversight procedures, are in line with the standard operating procedures of the Keele CTU and the conditions of the grant. Data is centrally monitored for quality and completeness by Keele CTU.

#### Data confidentiality and archiving

All information collected during the course of the trial is kept strictly confidential. Information is held securely on paper and managed electronically by Keele University through Keele CTU. Keele CTU comply with all aspects of the 1998 Data Protection Act. If a participant withdraws consent from trial intervention and/or further collection of data, their data will remain on file and is included in the final study analysis. At the end of the trial, data will be securely archived in line with the Sponsor’s procedures for a minimum of 5 years. Data held by Keele CTU will be archived in the designated Keele CTU archive facility and site data and documents will be archived at the participating sites. Following authorisation from the Sponsor, arrangements for confidential destruction will then be made.

#### Progress of the trial

Recruitment commenced in January 2016. Unfortunately, review of recruitment 3–6 months into the trial revealed that recruitment was sub-optimal and less than 50% of that predicted. Two key amendments were made (detailed in Table 1).

First on 19th August 2016 the eligibility criteria were amended. Criterion 3 was originally ‘Moderate-to-severe hip pain (a score of four or more on a 0-10 numeric rating scale (NRS)) on the day of assessment’. During the first 5 months of recruitment we observed that, due to the day-to day variability of osteoarthritis symptoms, a number of potential participants did not meet the eligibility criteria of pain of 4/10 on the day of assessment. The TSC suggested amending the criterion to ‘moderate to severe hip pain (a score of four or more on a 0-10 numeric rating scale (NRS)) on average over the last two weeks and current hip pain rated as at least one out of 10 (on a 0-10 NRS) on the day of assessment’. This amendment was approved by the DMC and Research Ethics Committee (REC). Forty-eight participants had been recruited at the time of this amendment.

Second, in March 2017, the Data Monitoring Committee noted poor recruitment and suggested rerunning the sample size calculations to ensure the original sample size assumptions were still valid. The observed baseline standard deviation (SD) of the primary outcome based on data collected from participants recruited by this time point (*n* = 65) was 1.7 (and the SD for follow up scores is around 2.5) – i.e. much lower than the SD of 4.5 expected before the start of recruitment on which the original sample size calculation was based. The clinically important difference of 1.5 (originally stated) in the context of this baseline SD would be ‘large’ (effect size above 0.8). The clinically important difference of 1.5 was considered to be too large in relation to the lower expected SD. The clinically important difference for the NRS-pain scale has taken different values across studies; an absolute difference of 1 has been specified in some studies (which would relate to a “moderate” effect size (0.5) when the SD is around 2; or, 0.4 in relation to higher SD of 2.5 which is observed across follow up time points). Hence, we felt that a revised effect size of 0.4 is justifiable. Using this revised effect size of 0.4 and revised power of 80% (on the advice of the TSC), the sample size was amended as described under ‘sample size’ heading, and was approved by the funder, TMC and DMC. A funded extension was requested, to extend recruitment from 18 months to 29 months, and approved in November 2017.

We removed a second qualitative objective to explore reasons for non-participation in the trial, to address any modifiable barriers to recruitment. This was in part due to limited capacity within the research team and low recruitment to this qualitative study of people who were eligible for the trial but unwilling to participate. All amendments have received ethical approval.

Recruitment via Route 3 commenced 12 months into recruitment and was noted to be more successful and became the principle route of recruitment from July 2017.

